### Outcomes

#### Primary outcome measures

The primary outcome will be the self-selected gait speed under fixed-priority dual tasks [18]. The walking speed was chosen as the primary outcome since it has been reported as an indicator of functional performance in older adults and a good predictor of physical performance [33–35], mortality [35], and falls [36–38].

For gait speed assessment, the participants will be asked to walk a leveled 30-m-long corridor twice (a total of 60 m) at a comfortable speed while barefoot. The initial and final 2 m (positive and negative acceleration, respectively) will not be considered for gait biomechanics analysis. Gait speed assessment will be described in the “Process A” section. This outcome will be assessed at all the time points.

#### Secondary outcome measures

Gait variables, functional mobility and balance tests, reactions time, confidence and fear of falls, quality of life, depression symptoms and fall episodes are the secondary outcomes and will be assessed at all the time points. These secondary outcomes presented in Table 3 were chosen because they represent the functional, biomechanical, and quality of life aspects of patients at risk for falls.

**Table 3 Tab3:** Schedule of forms and procedures of the study

				−1	0	T1	T2	T3	T4	T5
Activity/ Assessment	CRF (Y/N)	Staff member	Approximate time to complete	Pre-study screening/ consent	Pre-study baseline/ randomization	Study visit 1 immediately post-randomization	Study/ interim visit 2 (3 months)	Study/ interim visit 3 (6 months)	Post-intervention follow-up (3 months)	Post-intervention follow-up (6 months)
Pre-screening consent	N	Study Coordinator	5 min	X						
Screening log	N	Study Coordinator	5 min	X						
Inclusion/ exclusion form	Y	Study Coordinator	N/A	X						
Demographic data	Y	Interviewer	10 min		X					
Anthropometric data	Y	Assessor	5 min		X					
Gait speed, general, temporal and spatial variables	N	Assessor	15 min			X	X	X	X	X
Displacement of the body center of mass during *quasi*-static posture	N	Assessor	15 min			X	X	X	X	X
Functional balance tests	Y	Assessor	15 min			X	X	X	X	X
Mobility test	Y	Assessor	10 min							
Reaction time	Y	Assessor	10 min			X	X	X	X	X
Confidence and fear of falls	Y	Interviewer	10 min			X	X	X	X	X
Quality of life	Y	Interviewer	10 min			X	X	X	X	X
Depression symptoms	Y	Interviewer	10 min			X	X	X	X	X
Fall episodes	Y	Interviewer				Monthly				
Adverse events	Y	Study Coordinator	*N/A*			As needed throughout the protocol				
Adherence to the exercise program	Y	Interviewer				Monthly				

*CRF* Case report form, *N/A* Not applicable

### Participant timeline

The assessments will be performed at T1, T2, T3, T4, and T5. A 14-day window, defined as 7 days before and 7 days after the due date, will be available to complete the assessments.

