## Background

Older adults have an increased risk of falling, especially when they are required to perform a concurrent cognitive or secondary motor task while walking and carrying objects or paying attention to traffic [1–3]. In community-dwelling older adults this type of dual-task activity also significantly reduces gait speed [4] and increases gait variability [5–9]. Dual-task activities can be performed by shifting attention between tasks (dual task with variable-priority instructions) or placing equal amounts of attention on both tasks (dual task fixed-priority instructions) [10].

Regarding dual-task instruction priority, the literature has shown a bit more effect of training under variable- than fixed-priority instructions, although both are considered to have a great effect size [11]. These results are likely why participants trained under variable-priority instruction are able to learn faster and retain instruction better than dual-task training with fixed-priority instruction [12]. Nevertheless, we must consider that motor and cognitive tasks are often and simultaneously demanded in everyday situations, and so these tasks should be trained in protocols aiming for a dynamic postural balance in older adults. In addition, we can assume that fixed-priority instructions could be adopted as a progression of the variable-priority method since the learning and retention of the simultaneous motor and cognitive tasks of the former method appear more complex than the latter. Based on this rationale, in the first 12 weeks of training, both groups will be trained with dual-task activities exclusively under variable-priority instructions so that they can better learn and retain the motor and cognitive gains provided by this type of dual-task training, as already shown in the literature [12]. Over the next 12 weeks, only the participants in the control group will continue to evolve into the dual-priority variable task training. The experimental group will receive an exclusively dual-task training with fixed-priority, to better mimic most of the functional activities of daily living. To our knowledge, no research to date has attempted to prove this rationale.

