## Methods/design

### Study design

This is an assessor- and participant-blinded, two-arm, randomized controlled superiority trial. The study has been written according to the recommendations of the World Health Organization, the International Committee of Medical Journal Editors, the Consolidated Standards of Reporting Trials (CONSORT) [15], and the Standard Protocol Items (SPIRIT) statements [16, 17]. This trial was prospectively registered at ClinicalTrials.gov (NCT03886805).

Sixty community-dwelling older adults between the ages of 60 and 80 years old will be randomly assigned to either dual-task training with activities progression from variable- to fixed-priority attention (EG) or to dual-task training with variable-priority attention (CG) for 6 months. The assessments will be performed at baseline (T1), at 3 months of intervention (T2), at the end of the 6 months of intervention (T3), as well as at 3 (T4) and 6 (T5) months post-intervention (Fig. 1). The T2 assessment was established in order to verify any change after the period when the EG will be trained only with fixed-priority instructions and the CG will be keeping trained with variable priority instructions.

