### Intervention

The EG will be trained with variable-priority instruction activities during the first 3 months (T1 to T2) and in the subsequent 3 months (T2 to T3) will be submitted to training with fixed-priority instructions activities. The GC will be trained under variable-priority instruction activities over the 6 months (T1 to T3). The detailed evolution of each of the groups can be found in Tables 1 and 2.

**Table 1 Tab1:** Detailed conceptual basis regarding foci, tasks, and respective progressions to structure the training protocol

Focus	Strategy	Task
1. Postural balance	a) Change the base of support	**Standing** 1) Normal standing (bipodal support with feet separated at shoulder width 2) Feet together (bipodal support with feet side by side) 3) Semi-tandem stance 4) Tandem stance 5) One leg support on the dominant leg 6) One leg support on the non-dominant leg
		**Walking** 7) Semi-tandem 8) Tandem
	b) Displace the center of mass in different directions and with different bases of support	1) Sequentially perform F1a (1–6) by first laterally moving the trunk with shoulder abducted at least above 60 degrees 2) Sequentially perform F1a (1–6) by first laterally moving the trunk with the arms alongside the body
	c) Reach the body limits of stability and holding them at this point	1) Sequentially perform F1a (1–6) by first laterally moving the trunk with shoulder abducted at least above 60 degrees 2) Sequentially perform F1a (1–6) by first laterally moving the trunk with the arms alongside the body
	d) Change the somatosensation input (stability/complacency of the support surface)	Standing on different surfaces (rigid, soft or rough) 1) Sequentially perform F1a (1–6)
		Walking on different surfaces (rigid, soft or rough) 2) Sequentially perform F1a (7–8)
	e) Change the vision input	Standing with eyes closed 1) Sequentially perform F1a (1–6)
		Walking with eyes closed 2) Sequentially perform F1a (7–8)
2. Muscle strength and power, and postural balance during stationary activities performance	a) Standing still in a semi-squatting posture	1) Increase the time staying in this posture
	b) Weight-loaded in a single-leg stance	1) Gradually increase the standing time in this posture
	c) Sit to stand	1) Increase the number of cycles per seconds (starting at a frequency of one cycle per second)

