Note: *CG* Control group (dual-task training with variable priority attention), *EG* Experimental group (dual-task training with progression of activities from variable to fixed priority attention); ^a^Secondary cognitive or motor task will always be interspersed with dual tasks with variable priorities; ^b^Secondary cognitive or motor task will always be performed simultaneously with dual tasks with fixed priorities

Participants of both groups must attend at least 75% [26] of the 60-min training sessions, which will occur twice a week for 24 weeks. Each of the 48 group training sessions (maximum of 15 participants in each group) will include: i) a warm-up (10 min) with supervised walking on a flat surface and static postural balance exercises, ii) training (four stations, 10 min each, total of 40 min) for protocol execution, and iii) a cool-down, including breathing exercises and global muscle stretching (10 min). The principles of this training will follow recommendations from previous studies [26–29]. Interventions of each group will be supervised by a physical therapist with experience in ​​dual-task exercises and by four undergraduate students of the final year’s physical therapy course. Adherence monitoring will be done by signature in the presence table in each training session. Concomitant exercise programs for postural balance are not permitted during the trial for both groups.

The dual-task training program is designed based on activities described by Wollesen et al. [29] as well as the studies by Strouwen et al. [30] and Zhao and Pak-Kwongchung [31]. Table 1 presents the conceptual basis that will be used to structure the dual-task protocol training. The progression of the protocol will be based on eight foci (F1–F8), while strategies will progress in intensity and degree of difficulty; the tasks will be determined by associating the respective foci (F1–F8) with the strategies. This will allow for the graduation of the challenge level at each training stage regarding participants’ postural control and gait pattern.

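### The uniform ±7-day visit window lets T2 fall after the experimental group has begun fixed-priority training, against the phase boundaries that the Intervention section sets at T2 and T3

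*Protocol article*

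**What the plan says.** The visits are named in months. The Study design section places them "at 3 months of intervention (T2), at the end of the 6 months of intervention (T3"), followed by T4 and T5 at 3 and 6 months after the intervention. The Participant timeline section then applies one rule to all five: "A 14-day window, defined as 7 days before and 7 days after the due date, will be available to complete the assessments".

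The training is laid out in weeks. The Background section says that "in the first 12 weeks of training, both groups will be trained with dual-task activities exclusively under variable-priority instructions", and continues: "Over the next 12 weeks, only the participants in the control group will continue to evolve into the dual-priority variable task training". The Intervention section gives "60-min training sessions, which will occur twice a week for 24 weeks", 48 sessions in all. In Table 2, stage 4 (weeks 10 to 12) is the last stage shared by both arms. Stage 5 (weeks 13 to 15) is the first in which the EG's secondary tasks carry the fixed-priority mark. No testing interval separates the two.

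The Intervention section joins the two calendars. The EG receives variable-priority training "during the first 3 months (T1 to T2) and in the subsequent 3 months (T2 to T3) will be submitted to training with fixed-priority instructions". T2 and T3 are therefore the boundaries of the EG's fixed-priority phase.

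**The concern.** A window that extends 7 days past T2 permits what the phase definition excludes: an EG participant tested at T2 who has already had fixed-priority sessions. The same window applies to both arms, but the problem does not cancel, because only the EG changes its training in week 13. The primary outcome is gait speed under fixed-priority dual tasks, so those first sessions are practice in the tested condition, given to one arm.

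T2 is the only visit after baseline at which the arms should not differ, since training is identical until then. It is also the natural starting point for describing what happens once the arms diverge. The Statistical analyses section treats time as five levels, so a late T2 is pooled with an on-time one.

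A lesser question arises at T3, which is meant to mark the end of training but may be done before the last sessions or some time after them, depending on how a month is read.

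**Working it through.** **Inputs.** Two sessions a week for 24 weeks, window ±7 days, month labels (Intervention, Participant timeline, Study design); switch between weeks 12 and 13 (Background, Table 2). Days are counted from the start of training; this is an assumption, because the article does not state the origin of the due dates.

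**The plan's own figure.** 2 × 24 = 48 sessions, as stated. Each 12-week phase has 2 × 12 = 24 sessions. The variable-priority phase shared by both arms ends on day 12 × 7 = 84, and training ends on day 24 × 7 = 168. Seven days hold about 2 sessions.

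**Windows under each reading of the due date.** A calendar month is taken as 365.25/12 = 30.44 days.

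| Reading | T2 due | T2 window | Relative to day 84 | T3 due | T3 window | Relative to day 168 |
|---|---|---|---|---|---|---|
| 12 and 24 weeks | 84 | 77 to 91 | −7 to +7 | 168 | 161 to 175 | −7 to +7 |
| Calendar months | 91.3 | 84.3 to 98.3 | +0.3 to +14.3 | 182.6 | 175.6 to 189.6 | +7.6 to +21.6 |
| 13 and 26 weeks | 91 | 84 to 98 | 0 to +14 | 182 | 175 to 189 | +7 to +21 |

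**Fixed-priority sessions before T2 in the EG, at the latest permitted date** (days after 84 × 2/7).
- Week reading: 7 × 2/7 = 2 sessions; 2/24 = 8.3% of the phase.
- Calendar months: 14.3 × 2/7 = 4.1, about 4 sessions; 4/24 = 16.7%.

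**Average, if test dates are spread evenly over the window** (an assumption).
- Week reading: half of the dates precede day 84 and carry no exposure. The other half average 3.5 days, or 1 session. The mean is 0.5 × 1 = 0.5 session; 0.5/24 = 2.1%.
- 13 weeks: mean 7 days, 2 sessions; 2/24 = 8.3%.
- Calendar months: mean 7.3 days, 2.1 sessions; 2.1/24 = 8.7%.

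**Scale on the outcome.** The Sample size section takes 0.05 m/s as the minimal important difference. If an arm difference of that size accrued evenly over the fixed-priority phase (an assumption), the average part already present at T2 would be 0.05 × 0.021 = 0.001 m/s on the week reading and 0.05 × 0.087 = 0.004 m/s on the calendar-month reading.

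**T3.** On the week reading a participant may be tested with about 2 of 48 sessions still to come, or up to 7 days after the last. On the month reading every test falls about 1 to 3 weeks after training ends, and none before. Both apply to the two arms alike.

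**The case against.** A symmetric ±7 days is an ordinary visit window, and a condensed article may leave session-level booking to the full protocol. The article also seems to use months as shorthand for its own weeks: the same phase is 12 weeks in the Background and 3 months in the Intervention section. On that reading the overlap is at most a week and averages half a session. The randomised comparison at T3, or of change from T1 to T3, is unaffected by when T2 is done, and the Statistical analyses section does not single out change from T2 to T3 as the effect of interest. All of this stands, and it limits the size of the point.

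It does not remove the point. The window is stated, not omitted, and under every reading it admits T2 tests after the switch.

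A reader might infer more, and the document does not support it:
- *That T2 and T3 are not tied to the training phases.* They are, in words, in the Study design and Intervention sections. It is the window and the unit of the due dates that fail to respect the tie.
- *That T3 can vary over 28 days.* That figure sets the earliest date of the week reading (161) against the latest of the month reading (189). Within either reading the spread is 14 days.
- *That the effect loses 8–17%.* Those are latest-date maxima under even accrual, not expected losses.
- *That whole classes, and so arms, will be booked differently.* Nothing in the text indicates this.

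**Conclusion.** The uniform window conflicts with the phase boundary at T2. The overlap touches one arm only and concerns the condition in which the primary outcome is measured. Average exposure before T2 is about 2% of the fixed-priority phase if the due date is week 12, and 8–9% if it is a calendar date. The maxima are about 2 and about 4 of 24 sessions. These figures rest on counting from the start of training and, for the averages, on evenly spread test dates. The true bias in any T2 contrast cannot be computed from the document and is probably small on the week reading.

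The T3 comparison between arms is not threatened by T2 timing, and no sample-size figure changes. The looseness at T3 itself is common to both arms, so it is mainly noise. This is a modest inconsistency that is worth correcting because the correction costs little.

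**What to change.** State the due dates in training weeks (end of week 12 for T2, end of week 24 for T3), and keep the 14-day length but make it one-sided at the phase boundaries, identically in both arms:
- **T2:** within the 14 days up to the participant's first week-13 session, and never after it.
- **T3:** within the 14 days after the last scheduled week-24 session, and never before it.
- **T4 and T5:** keep ±7 days, counted from the last scheduled session.

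Confining T2 to the gap between the last week-12 session and the first week-13 session would be too tight. That gap is only a few days, and the timed T2 procedures in Table 3 add up to about 85 minutes per participant, or about 21 hours for a class of 15 (15 × 85/60 = 21.25). The one-sided 14 days leaves the booking period as long as it is now and needs no extra staff.

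The cost is small. Some T2 tests will precede the last variable-priority sessions (up to about 4 of the first 24, since 14 × 2/7 = 4), equally in both arms. Some T3 tests will come up to two weeks after training. A T2 not done before week 13 counts as outside the window.

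The Study design section also says that T2 serves to check change after the EG's fixed-priority period, whereas the Intervention section puts that period after T2. The two passages should be reconciled in the same edit.

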#### Data collection, management, and analysis

Two assessors ([name] and [name]) will carry out all the data collection, management, and analysis. Both evaluators were submitted to a previous and extensive training protocol for data collection, management, and analysis. Clinical and functional data will be collected by [name] and biomechanics data by [name]. Double data entry will be done interchangeably by both assessors.

#### Process A: biomechanical analysis

Three Physilog® sensors (Gait Up, Lausanne, Switzerland) will be used in this study for biomechanical analysis of all functional activities. Physilog® is an inertial measurement unit (IMU) based on a standalone device (dimensions: 50 mm × 40 mm × 16 mm; weight: 36 g) including a tri-axial accelerometer (MMA7341LT, range ± 3 g, Freescale, Austin, TX, USA), a tri-axial gyroscope (ADXRS, range ± 600°/s, Analog Devices, Norwood, MA, USA), a battery (3.7 V, 595 mAh), a memory unit, and a microcontroller.

To measure gait spatiotemporal and foot clearance variables during the single and dual tasks (under variable and fixed priorities), two IMUs will be attached to the feet’s torso with a neoprene strap. Using a hypoallergenic neoprene belt, a waist-worn sensor will be fixed around the participant’s waist to measure tri-axial acceleration and angular velocity data. Prior to gait data acquisition, the participant will have a period to habituate to the laboratory environment. The participant will be asked to walk in the usual way (as carried out in his/her daily activity) on a 30-m walkway (go and come back) at her/his preferred walking speed and discretion [39, 40]. For the gait analysis, the two first strides performed at the beginning and end of the gait test will be excluded (the positive and negative acceleration phases, respectively) [41].

The tri-axial acceleration and angular velocity data will be acquired using the waist-worn sensor while performing (i) a quasi-static posture during the clinical test of sensory interaction and balance (CTSIB), (ii) the Stroop test during quasi-static posture, (iii) the timed up and go (TUG) test (conventional, manual, and cognitive), (iv) the functional anterior reach test, (v) and the sit-and-up from the floor and from a chair test (five times). Prior to the data acquisition, the evaluator will demonstrate the tests to the participant.

All kinematics data (tri-axial acceleration and angular velocity) will be sampled on an on-board 16-bit analog-digital converter at a sampling frequency of 128 Hz. All signals from the three Physilog® sensors will be synchronized by wireless transmission and recorded on a micro SD card inside the IMU before being transferred to a computer. The waist-worn sensor data will be filtered using a 4-th order infinite impulse response (IIR) low-pass Butterworth filter with a cut-off frequency of 5 Hz [42].

The gait variables acquired by both feet-worn sensors will be analyzed by the gait analyzer software (Gait Up, Lausanne, Switzerland). The complexity of multivariate signals over multiple temporal scales acquired by the waist-worn sensor (during gait and quasi-static conditions) will be analyzed by refined composite multivariate generalized multiscale fuzzy entropy using a Matlab routine (Mathworks, Inc.; Natick, MA) developed by Azami and Escudero [43].

#### Process B: assessment of functional balance, fall events, quality of life, and depression symptoms

The following functional capacity tests will be assessed: gait speed [10], spatiotemporal gait biomechanics, TUG_Conventional_ [44], TUG_Cognitive_ [45], TUG_Manual_ [45], postural balance test [46], sit-and-up (from the floor) [47], sit-and-up (from a chair) [48], anterior functional reach test [49], CTSIB [50], Falls Efficacy Scale–International [51], and Activities-specific Balance Confidence scale [52].

In order to evaluate suggestive depression symptoms and quality of life, the Brazilian Short Form of the Geriatric Depression Scale [53] and the Brazilian Medical Outcomes Study 36-Item Short-Form Health Survey, respectively, will be used [54]. Process B will be carried out by two physical therapists ([name] and [name]) with previous experience in functional balance and emotional and quality of life assessment in older adults.

#### Process C: evaluation of the number of falls

Each patient will receive a diary to record the date, time, place, and reason for a fall as well as any injury or form of treatment after the episode. This diary will be collected monthly until the end of the study.

### Statistical analyses

Statistical analyses will be performed based on the intention-to-treat principle. The independent variables of the clinical trial will be both groups (two levels) and the time, counted in weeks (five levels; T1 to T5).

The pattern of missing data will be previously analyzed [55]. A full description of the reasons for possible sample losses will be presented after the end of the study. Exploratory analyses will be performed to verify the distribution of variables, identification of outliers, missing data, and asymmetries.

Generalized Estimation Equations (EEG) will be used for univariate analyses, considering the factors group (EG and CG) and time (T1, T2, T3, T4 and T5), as well as the interaction effect (time vs. group). The most appropriate GEE model for each variable will be confirmed by considering the measurement scale, the Quasi-likelihood Information Criterion (QIC) values, the working correlation matrix, the data distribution, and the respective log link.

Adjustments for univariate (main effects) and multivariate (interaction effect) comparisons of estimated marginal means (EMM) will be made by the Sidak test.

A 95% confidence interval for the mean difference that lies entirely on the EG side will be considered a superiority result statistically significant.

The Statistical Package for the Social Sciences (SPSS, IBM; v.22.0) will be used for statistical analyses.

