### Sample size

Gait speed (primary outcome) under fixed-priority dual tasks was used to calculate the sample size [18]. We adopted a minimal clinically important difference of 0.05 m/s, an effect size of 0.20 [19], a power of 95% (1 - β), an alpha of 0.05, and a design of *F*-statistic repeated measures with a within- and between-subjects interaction effect. Forty-eight participants were initially obtained as the study sample total. Taking into account a 20% sample loss, 60 participants will be assessed and allocated to the study by a ratio of 1:1. The sample size was calculated using the G*Power 3 [20].

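### The planned GEE for gait speed has no baseline covariate, leaves link and correlation to the data, and does not define the mean difference that decides superiority

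*Protocol article*

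**What the plan says.** All of this stands in the protocol article, mostly under Statistical analyses.

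- **Model terms:** "Generalized Estimation Equations (EEG) will be used for univariate analyses, considering the factors group (EG and CG) and time". The five assessments from T1 to T5 are the levels of time, and the model also carries the group-by-time interaction. No baseline covariate is listed, so T1 is one of the five outcome levels.
- **Model choice:** "The most appropriate GEE model for each variable will be confirmed by considering the measurement scale, the Quasi-likelihood Information Criterion (QIC) values". The list of criteria continues with the working correlation, the data distribution and the link. This is done variable by variable, with no exception for the primary outcome.
- **Comparisons:** "comparisons of estimated marginal means (EMM) will be made by the Sidak test", for main effects and for the interaction.
- **Decision rule:** "A 95% confidence interval for the mean difference that lies entirely on the EG side will be considered a superiority result statistically significant". Neither the visit nor the type of difference (means at a visit, or changes from T1) is given.
- **Size:** Under Sample size, 48 participants are required on a repeated-measures F test of the within-between interaction. Then: "Taking into account a 20% sample loss, 60 participants will be assessed and allocated to the study by a ratio of 1:1". That is 24 evaluable and 30 randomised per arm.

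The test statistic, the type of standard error and any small-sample correction are not stated.

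**The concern.** Three features fit poorly with a trial of this size.

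1. **Baseline.** Gait speed is measured at T1 and is likely to predict later gait speed. With T1 as an outcome level, the EG-CG difference in marginal means at a later visit is unadjusted, so chance imbalance at T1 passes into it. The interaction does remove T1, but by subtraction, which is less precise than adjustment. Because the decision rule does not say which difference counts, the reader cannot tell which of the two applies.

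2. **A primary model settled on outcome data.** The rule needs a difference in means, and the minimal important difference under Sample size is 0.05 m/s. A log link would give a ratio of means instead. The working correlation also matters if dropout depends on earlier gait speed: unweighted GEE is then protected only if that structure is right.

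3. **Small samples.** GEE is commonly tested with sandwich standard errors and a chi-square or normal reference. With 24 to 30 per arm this rejects too often unless corrected.

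At stake are avoidable loss of power, some excess type I error, and analyst choice in the primary result.

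**Working it through.** **The plan's own figure.** Inputs from Sample size: effect size 0.20 (read as Cohen's f), alpha 0.05, power 95%. Assumed, because not stated: five measurements, correlation 0.5, sphericity. Noncentrality = f² × N × m / (1 − ρ) = 0.04 × 48 × 5 / 0.5 = 19.2, with df 4 and 184. Power is 0.952 at N = 48 and 0.942 at N = 46. With 20% loss, 48 / 0.8 = 60. The stated 48 and 60 reproduce, so the sample size itself is not in question.

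**Baseline adjustment.** The correlation r between T1 and the later visit is not given; 0.5 and 0.7 are assumed. Relative to the variance of the unadjusted visit difference (set to 1), the change contrast has variance 2(1 − r) and the baseline-adjusted contrast 1 − r². Adjusted over change is therefore (1 + r)/2.

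| r | change | adjusted | saving vs visit difference | saving vs change |
|---|---|---|---|---|
| 0.5 | 1.00 | 0.75 | 25% | 25% |
| 0.7 | 0.60 | 0.51 | 49% | 15% |

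Power for an illustrative 0.4 SD difference, 24 per arm, r = 0.7, by the normal approximation Φ(0.4 × √(24/2) / s − 1.96), where s is the square root of the relative variance and 0.4 × √12 = 1.386:

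- visit difference, s = 1: Φ(−0.574) = 28%
- change, s = 0.775: Φ(−0.171) = 43%
- adjusted, s = 0.714: Φ(−0.020) = 49%

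**Small-sample error.** Assumed: normal data, no missing values, uncorrected sandwich variance. For a saturated group-by-time model that variance is (n − 1)/n times the unbiased one.

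- *One contrast:* reject when |t| > 1.96 × √((n − 1)/n) on 2n − 2 df. At n = 24 the cut-off is 1.919 on 46 df and the error is 6.1%. At n = 30 it is 1.927 on 58 df and the error is 5.9%. Against the t critical values 2.013 and 2.002, intervals are 4.7% and 3.7% too narrow.
- *4-df interaction:* reject when F > 9.488 × (n − 1)/n × (2n − 5) / [4(2n − 2)] on 4 and 2n − 5 df. At n = 24 the cut-off is 2.125 and the error is 9.4%. At n = 30 it is 2.174 and the error is 8.4%.

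Simulation with complete data (3,000 runs per setting, correlation 0.6) gave 6.2% to 6.3% for one contrast and 8.9% to 9.3% for the interaction.

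**Working correlation and dropout.** Simulated with 30 per arm, no treatment effect, correlation 0.6, and dropout driven by the previous value (about 18% lost by T5).

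| dropout | true structure | working structure | bias at T5 (SD) |
|---|---|---|---|
| opposite directions by arm | exchangeable | exchangeable | 0.004 |
| opposite directions by arm | exchangeable | independence | 0.24 |
| opposite directions by arm | AR(1) | exchangeable | −0.09 |
| same in both arms | exchangeable | independence | about 0 |

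The second row, where the single-contrast error is 15.6%, is a deliberately adverse case.

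**The case against.** GEE with group, time and interaction is an accepted longitudinal analysis, and several stronger readings go beyond the article.

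- **That the plan simply compares raw arm means.** A reader might infer this from the missing covariate. But T1 and the interaction are both in the model, the interaction is a contrast of change from T1, and the trial was sized on that interaction. Savings of up to 49% therefore hold only if the decision rests on a visit difference. What stands is that the rule leaves this open and that adjustment gains precision either way.
- **That the plan relies on large-sample Wald tests.** The article names no test statistic or type of standard error. Such details may stand in an analysis plan that is not shown, so the error rates above are conditional.
- **That error is inflated to 8% to 9% for the decision.** That figure belongs to the 4-df omnibus test. The stated rule uses an interval for one difference, where the error is about 6%. Under a Sidak adjustment over five visit-wise arm contrasts (an assumed family, per-test level 1 − 0.95^(1/5) = 1.02%), the formula above gives 1.5% and 1.4% for any one contrast at 24 and 30 per arm. Sidak does not repair the standard errors, and the article does not say whether the decision interval is Sidak-adjusted.
- **That dropout will bias the result.** Losing the slowest 20% from one arm only would shift available-case means by 0.175 SD at r = 0.5 (0.35 × 0.5), but nothing in the article makes that mechanism expected. Its conversion to m/s needs a standard deviation that the article does not give. With the right working correlation, or the same mechanism in both arms and no effect, bias was about zero. The absence of a missing-data method is no finding here.
- **That GEE must be replaced.** This is partly preference; a corrected, baseline-adjusted GEE would also answer the main points.

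**Conclusion.** The concern holds in limited form. The article lists the model terms without a baseline covariate, allows the gait-speed model to be settled on outcome data, and ties superiority to an undefined difference. Adjusting for a measurement already collected would save 25% to 49% of variance if the decision rests on a visit difference. It would save 25% (r = 0.5) or 15% (r = 0.7) if it rests on change. The correlations are assumed. If uncorrected sandwich inference is used, the excess error is mild for a single contrast (about 6%) and material only for the 4-df interaction (8% to 9%), assuming normal, complete data. Dependence on the working correlation is a risk under arm-differential dropout, not a predicted bias. None of this invalidates the trial, but it should be corrected before analysis.

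**What to change.** For gait speed, prespecify one identity-link model in m/s:

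- T1 speed as a covariate with its interaction with visit, or a constrained-baseline model;
- a named primary EG-CG contrast, for example at T3, as the mean difference in the decision rule, with a statement of whether its interval is Sidak-adjusted;
- a small-sample correction;
- no choice of the primary model by QIC.

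A mixed model for repeated measures meets this: REML, unstructured covariance, Satterthwaite or Kenward-Roger degrees of freedom, all randomised participants included. Under MAR dropout it does not depend on a working correlation picked by QIC. GEE with a small-sample correction can stay for counts and ordinal outcomes, or as a sensitivity analysis.

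The cost is a change of analysis text and slightly more analysis work. No new data or participants are needed. The downside is that an unstructured covariance may not converge at this size, so the fallback structure should be named in advance.
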